## Introduction

### Background and rationale {6a}

Vitamin D3 (cholecalciferol) is produced by the human skin from its precursor 7-dehydrocholesterol, or received from diet. Initially, cholecalciferol undergoes 25-alpha hydroxylation in the liver, forming calcidiol. Another hydroxylation takes place primarily in the kidneys, where calcidiol is metabolized to calcitriol by 25-hydroxyvitamin D3-1α-hydroxylase. The crucial physiological effect is to increase serum calcium levels by stimulating renal calcium retention, intestinal calcium resorption, and bone resorption to maintain normocalcemia. Calcitriol predominantly affects bone, tooth, and cartilage mineralization indirectly by regulation of local calcium and phosphate levels; however, there is also direct action on mineralization as calcitriol has genomic and non-genomic effects on cells of mineralizing tissues [1]. Calcitriol binds to the vitamin D nuclear receptor (VDR). VDRs, present in many tissues, are involved in the expression of more than 500 of the total 20,488 genes in the human genome [2]. The 25-OH hydroxyvitamin D (calcidiol) with its elimination halftime of 15 days is the best indicator of the vitamin D saturation state in the body, as it takes into account both vitamin D3 produced endogenously in the skin and exogenous vitamin D2 and D3 from the diet. The definition of individual vitamin D saturation status based on blood calcidiol concentration is controversial [3]. For the purposes of our clinical trial, we have defined it as displayed in Table 1, with a value for serum calcidiol of 80 nmol/L as the low end of the optimal range. Serum calcidiol below this level results in impaired calcium absorption and carries a risk of bone loss and osteoporotic fractures [4, 5].

**Table 1 Tab1:** Definition of vitamin D saturation status based on serum calcidiol levels

Serum calcidiol concentration in ng/mL and nmol/L, respectively		Vitamin D saturation status—interpretation of values
< 10 ng/mL	< 24 nmol/L	Deficiency
10–20 ng/mL	25–49 nmol/L	Insufficiency
20–30 ng/mL	50–74 nmol/L	Sufficiency
30–50 ng/mL	75–125 nmol/L	Optimal level (considered for this clinical trial)
> 100 ng/mL	250 nmol/L	Risk of toxicity

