### Criteria for discontinuing or modifying allocated interventions {11b}

No interventions or drug dose changes will be made during the trial. If there is any problem related to the clinical trial, patient participation in clinical trial will be terminated. The decision for termination can be made from both sides:
Patient decisionA trial participant may leave the trial at any time without providing a reason.Examiner decisionDue to the fact that the clinical trial is based on the administration of cholecalciferol or placebo, termination of the clinical trial by the investigator is very unlikely. Nevertheless, in rare circumstances described below, the examiner may decide to exclude a subject from the trial due to preventive reasons.

Criteria for the clinical trial discontinuing by examiner:
Cholecalciferol intoleranceHypercalcemia—serum total calcium concentration higher than 2.75 mmol/L, measured in at least one of the scheduled laboratory testsHyperphosphatemia—concentration of total phosphorus in the serum above 1.61 mmol/L, measured in at least two of the scheduled laboratory testsAn increased serum alkaline phosphatase activity two times higher than the physiological range, measured in at least two of the scheduled laboratory testsA high level of calcidiol above 200 nmol/L, measured in a targeted manner in case of suspected overdose at any time during CTThe need to use prohibited medicationPregnancy

Interruption or termination of CT for other reasons is always subject to the judgment of the examiner (medical doctor), but due to its design is not expected.

In both decisions of this participant’s termination, trial subject will be asked to do the following:
To return the rest of the IMP at the hospital Cardiac Surgery DepartmentTo be medically examined within 14 days from the medication withdrawal (calcidiol concentration, calcium concentration)—these examinations can also be requested by a general practitioner in the place of trial subject residence

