#### Safety outcomes

Safety endpoints related to impaired biochemical examinations, calculated incidence in two parallel patient groups with cholecalciferol or placebo treatment:
Serum calcium concentration out of physiological range (values within the range 2.05–2.9 mmol/L considered physiological)Alkaline phosphatase activity out of physiological range (values within the range 0.66–2.2 μcat/L considered physiological)Serum phosphate concentration out of physiological range (values within the range 0.65–1.61 mmol/L considered physiological)Endpoints related to non-serious adverse effects, calculated incidence in two parallel patient groups with cholecalciferol or placebo treatment:
ConstipationLoss of appetiteNauseaOther non-serious adverse effectEndpoints related to serious adverse events, calculated incidence in two parallel patient groups with cholecalciferol or placebo treatment:
DeathLife-threateningHospitalization (initial or prolonged)Disability or permanent damageRequired intervention to prevent permanent impairment or damage (devices)Important medical event

Efficacy and safety endpoint evaluation timetable is shown in Table 3.

**Table 3 Tab3:** Efficacy and safety endpoint evaluation timetable

Week	Examination of the subject by the investigator	Laboratory examination of the subject	Evaluation of subject’s quality of life	Imaging examination of the subject
**0**	**Initial interview with the patient + initial medical examination + decision to offer clinical trial participation to the patient**	**Initial complete biochemical examination including monitored parameters (calcium, phosphate, calcidiol, and ALP)**	**Acquaintance with the trial + provision of signed informed consent**	
**1**		**Continuous determination of several biochemical parameters during hospitalization: serum calcium (minimally every other day), ALP values (minimally once during hospitalization), and serum phosphate (minimally once during hospitalization)**		
**2**	**Examination of the surgical wound before hospital discharge**	**Laboratory tests before discharge**		
**6**	**Continuous examination of surgical wound**	**Continuous evaluation of serum calcium, ALP, and phosphate**		
**26**	**Exit examination of the surgical wound**	**(1) Final lab. test of serum calcium, ALP, and phosphate; (2) calcidiol level; (3) doctor’s entry in Questionnaire No. 1**	**Final evaluation of quality of life according to Questionnaire No. 2**	**Computed tomography of the chest**

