## Data collection and management

### Plans for assessment and collection of outcomes {18a}

Different outcome investigators are responsible for data collection and assessment (trial examiners, trial clinical biochemist, trial clinical radiologist, trial pharmacists, and trial administrative workers).

There are two electronic databases: Database No. 1 (central trial register) with access for all trial workers except the pharmacist, and Database No. 2 (information about IMP content) with an access restricted to the pharmacist and independent clinical pharmacist.

Trial data from laboratory tests will be copied from hospital patient medical records and stored in one database (Database No. 1) at the end of the clinical trial.

Two paper questionnaires will be used: Questionnaire No. 1 for medical doctor reporting clinical findings and Questionnaire No. 2 for the trial participants. Patient questionnaires and medical assessment questionnaires will primarily be hard copy (paper version), and the data from them will be manually transferred to the central electronic database.

The main clinical trial coordinator is also responsible for clinical trial monitoring.

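### The calcium safety endpoint treats values up to 2.9 mmol/L as normal, although the protocol's own limit for hypercalcemia is 2.75 mmol/L

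*Protocol article*

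**What the plan says.** Three parts of the protocol article bear on calcium.

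- **Safety outcomes** introduces the laboratory endpoints as "Safety endpoints related to impaired biochemical examinations, calculated incidence in two parallel patient groups with cholecalciferol or placebo treatment". The calcium endpoint is "Serum calcium concentration out of physiological range (values within the range 2.05–2.9 mmol/L considered physiological"). The phosphate endpoint is "Serum phosphate concentration out of physiological range (values within the range 0.65–1.61 mmol/L considered physiological").
- **Criteria for discontinuing or modifying allocated interventions {11b}** lists hypercalcemia, specified as serum total calcium above 2.75 mmol/L on one scheduled test. The list is discretionary: "the examiner may decide to exclude a subject from the trial due to preventive reasons". A participant who leaves is asked to return the remaining medication and to "be medically examined within 14 days from the medication withdrawal (calcidiol concentration, calcium concentration").
- **Interim analyses {21b}** repeats the 2.75 mmol/L criterion.

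Table 3 schedules calcium at baseline, during the hospital stay ("serum calcium (minimally every other day")), before discharge, and at weeks 6 and 26. Section {18a} states: "Trial data from laboratory tests will be copied from hospital patient medical records and stored in one database".

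**The concern.** The same calcium value can be hypercalcemia under the discontinuation rule and physiological under the safety endpoint. Both numbers are printed in this article, so this is not a detail left to an analysis plan that is not shown.

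What is at stake is how one laboratory safety result will read. The protocol regards hypercalcemia as reason enough, on a single test, to consider stopping treatment. Yet the incidence chosen to compare calcium between the arms leaves out the part of hypercalcemia nearest the limit. A patient stopped at 2.80 mmol/L also has less opportunity to reach a value above 2.9 later, because medication ends and the article describes only one further calcium check. A reader of the final table could take the reported incidence as covering hypercalcemia as the trial defines it, and it would not.

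**Working it through.** There is no stated figure to reproduce. The check is to apply both rules to the same values.

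**Inputs**
- Rule A ({11b}, {21b}): hypercalcemia if calcium > 2.75 mmol/L on at least one test.
- Rule B (Safety outcomes): endpoint event if calcium < 2.05 or > 2.90 mmol/L.

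Rule A says total serum calcium and Rule B says serum calcium. The article describes no other calcium measure, so I take them to be the same assay.

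**Classification of single values**

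| Calcium (mmol/L) | Rule A: hypercalcemia | Rule B: counted now | Counted if upper limit is 2.75 |
|---|---|---|---|
| 2.04 | no | yes (low) | yes (low) |
| 2.05 | no | no | no |
| 2.75 | no | no | no |
| 2.76 | yes | no | yes |
| 2.80 | yes | no | yes |
| 2.90 | yes | no | yes |
| 2.91 | yes | yes | yes |

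Width of the discordant band: 2.90 − 2.75 = 0.15 mmol/L. Relative to the hypercalcemia limit: 2.90 / 2.75 − 1 = 0.055, or 5.5%.

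**Per-patient count.** For each patient let M be the highest and m the lowest post-baseline calcium. In each arm:
- hypercalcemia as the protocol defines it = number with M > 2.75;
- endpoint as written = number with m < 2.05 or M > 2.90;
- hypercalcemic patients missed by the endpoint = number with 2.75 < M ≤ 2.90 and m ≥ 2.05.

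A patient in the band who also has a low value is counted, but on account of the low value. If no patient has M in the band, the endpoint count is unaffected.

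**Comparison with the other two analytes**

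| Analyte | Endpoint upper limit | Discontinuation limit | Tests needed to stop | Stopping ÷ endpoint limit |
|---|---|---|---|---|
| Alkaline phosphatase | 2.2 | twice the range, read as 2 × 2.2 = 4.4 | two | 2.00 |
| Phosphate | 1.61 | 1.61 | two | 1.00 |
| Calcium | 2.9 | 2.75 | one | 2.75 / 2.9 = 0.95 |

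Only for calcium does the stopping limit lie inside the range called physiological.

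**Which patients enter the count.** Section {20c} removes from the final evaluation any participant with missing primary endpoint data. A patient withdrawn at 2.80 mmol/L may have no 6-month wound assessment. If that exclusion also governs the safety tables, lowering the limit alone would not bring this patient into the incidence. The analysis set has to be stated with the limit.

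**The case against.** The strongest reply is that an action limit and an endpoint limit serve different purposes and need not agree. Alkaline phosphatase shows that the protocol does not tie them together, so the match for phosphate proves little by itself. This is correct as far as it goes. But for alkaline phosphatase the endpoint is the more sensitive of the two, which is a coherent order. For calcium the order is reversed, and a value labelled hypercalcemia falls within the range labelled physiological. The 2.9 may be a deliberate laboratory limit; the article does not say, so what can be asserted is an unreconciled inconsistency and not which number is the mistake.

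The reply that little is lost also has force. Stopping is at the examiner's discretion, so a patient at 2.80 mmol/L need not leave. The values remain in the database and may also surface as adverse events or withdrawals. Further tests beyond the 14-day check are not ruled out. All of this stands, and it limits the point to one stated endpoint.

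Four stronger readings are tempting and should not be drawn:

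- **That the protocol predicts raised calcium as a harm.** The background says "The crucial physiological effect is to increase serum calcium levels", but that sentence goes on to say that the purpose is to keep calcium normal. It describes physiology. The reason to count values above 2.75 is that the protocol itself makes them a stopping criterion.
- **That pooling low and high calcium in one incidence is an error.** All three laboratory endpoints are two-sided. Splitting them by direction is a tabulation choice that an analysis plan can make.
- **That most hypercalcemia would be missed, or that an excess in the active arm is hidden.** The article gives no calcium distribution. Any such share would come from an assumed one.
- **That patients could enrol when already above 2.75 mmol/L.** The inclusion criterion requires calcium in the physiological range but gives no numbers, so it cannot be said that the 2.05–2.9 range governs entry.

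**Conclusion.** The inconsistency is certain from the text. Followed as written, the per-arm calcium incidence omits patients whose highest calcium is above 2.75 and up to 2.90 mmol/L, unless they also have a value below 2.05. The endpoint can therefore under-count hypercalcemia by the protocol's own definition. The number affected is unknown and may be zero. No data are lost, and no efficacy result, sample size or eligibility decision is touched. The conclusion assumes only that both sections refer to the same calcium measurement. It is a modest point about one safety table, worth correcting because the correction is cheap and can be made before anyone has seen results by arm.

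**What to change.** Before unblinding:

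1. Set the upper limit of the calcium safety endpoint at 2.75 mmol/L. If 2.9 is a deliberate laboratory limit, keep it and say so.
2. In either case, report per arm the number of patients with any post-baseline calcium above 2.75 mmol/L, taken from the stored laboratory data.
3. State the analysis set for that count: all randomised patients who received trial medication, including those withdrawn and those lacking primary endpoint data, so that the exclusion in {20c} does not remove them.

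The cost is one extra row in a safety table. No new measurement is needed, because the Table 3 schedule already supplies the calcium values. If the limit itself is changed while the trial is running, section {25} requires an amendment to the ethics committee, with registration and a report to the national regulator. Treatment and eligibility stay as they are.

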### Trial design {8}

This clinical trial is conducted as a monocentric, randomized, double-blind, placebo-controlled trial, with the goal to enroll 600 patients over 4 years: approximately 300 subjects in the placebo arm and 300 in the treatment arm. Males and females aged 18 to 95 years who fulfill the indication criteria for undergoing cardiac surgery with sternotomy may be included in this clinical trial, if they meet the eligibility criteria (as shown in Table 2).

**Table 2 Tab2:** Patient eligibility criteria

Inclusion criteria	Exclusion criteria
Patient:	Patient:
• Undergoing cardiac surgery with sternotomy	• With known hyperparathyroidism
• With baseline calcium, phosphate, and alkaline phosphatase values in physiological ranges	• Treated or supplemented by vitamin D or its derivatives (alfacalcifediol, calcitriol, paricalcitol) including ergocalciferol (vitamin D2) when used regularly for 3 months before entering the trial
• With sufficient ability to understand and cooperate in planned medical examinations	• Undergoing repeated sternotomy
• Czech or Slovak speaker with permanent residence and citizenship in the Czech Republic	• With chronic renal insufficiency associated with osteodystrophy (hyperphosphatemia, hypocalcemia)
• With initial calcidiol levels less than 75 nmol/L	• With severe hepatic impairment associated with cirrhosis, Child-Pugh score B and C
• With signed informed consent to enter the trial	• With known metabolic bone disease
• Male or female between 18 and 95 years of age	• With cancer associated with primary or secondary risk of bone damage
	• With known immunodeficiency
	• With short bowel syndrome or other malabsorption syndrome that limits absorption of lipophilic vitamins
	• With long-term cardioactive glycoside and/or thiazide diuretic treatment that cannot be replaced with alternative treatment during cardiac surgery hospitalization
	• Prior to the planned radiotherapy affecting the body skeleton
	• With known allergic reaction or intolerance to IMP
	• With long-term teriparatide treatment or other parathyroid hormone
	• With long-term bile acid sequestrant treatment which cannot be replaced by any other treatment during cardiac surgery hospitalization
	• With long-term corticosteroid treatment or other immunosuppressive drugs
	• With another medical condition which the investigator considers a risk for the patient during the trial

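### Biochemical safety is summarised only as the share of patients outside a range, high and low counted together, which would miss most systematic shifts in phosphate or ALP

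*Protocol article*

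**What the plan says.** Under Outcomes {12}, Safety outcomes, the biochemical endpoints are introduced as "Safety endpoints related to impaired biochemical examinations, calculated incidence in two parallel patient groups with cholecalciferol or placebo treatment". Three analytes follow in the same form:

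- phosphate: "Serum phosphate concentration out of physiological range (values within the range 0.65–1.61 mmol/L considered physiological"
- ALP: "Alkaline phosphatase activity out of physiological range (values within the range 0.66–2.2 μcat/L considered physiological"
- calcium: "Serum calcium concentration out of physiological range (values within the range 2.05–2.9 mmol/L considered physiological"

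Each range has a lower and an upper limit, and a value beyond either one counts. No direction, size of change or baseline value enters the definition.

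The baseline appears in Table 2 as an inclusion criterion: "With baseline calcium, phosphate, and alkaline phosphatase values in physiological ranges". Table 3 shows that calcium, phosphate and ALP are measured at week 0 and again later: in hospital ("ALP values (minimally once during hospitalization), and serum phosphate (minimally once during hospitalization"), before discharge, at week 6 ("Continuous evaluation of serum calcium, ALP, and phosphate") and at week 26 ("Final lab. test of serum calcium, ALP, and phosphate").

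Statistical methods {20a} assigns a chi-square test to the primary endpoint and t tests to the secondary endpoints. It names no test for the safety endpoints, and no expected rate, SD or power is given for them.

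**The concern.** Cholecalciferol acts on calcium and phosphate handling and on bone, so a modest shift of the whole distribution is a plausible way for a biochemical effect to appear. A patient whose phosphate moves from 0.80 to 1.55 mmol/L adds nothing to the count, while one who moves from 1.58 to 1.63 adds a full event. If the drug moves values upwards, some patients cross the upper limit and others stop falling below the lower one. With both directions in one count, these changes partly cancel.

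At stake is how a finding of similar incidences would be read. The article plans no interim analysis and no data monitoring committee, so the end-of-trial summary is the planned between-arm look at biochemical safety. Similar incidences could be taken as evidence that the drug does not move phosphate or ALP, when the summary could hardly have shown it.

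**Working it through.** **Plan's own figure.** There is none for these endpoints. The only calculated design figure, 284 per arm, concerns sternotomy complications and has no bearing here.

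**Inputs from the document.** Phosphate range 0.65–1.61 mmol/L; about 300 patients per arm; in-range baseline required; four post-baseline values (in hospital, before discharge, week 6, week 26).

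**Assumptions not in the document.** Phosphate is normal and centred in the range, at (0.65 + 1.61)/2 = 1.13. The entry limits equal the safety range. The range spans 3.92, 5 or 6 SD of a single value. Within-person CV is 5–15%. There is no surgical shift. A patient counts if any of the four values is out of range. Comparisons are two-sided at 5%.

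- Total SD = 0.96/3.92 = 0.245, 0.96/5 = 0.192, or 0.96/6 = 0.160.
- Within-person SD = 1.13 × CV: 0.057 at 5%, 0.170 at 15%. (15% cannot be combined with the 6 SD range, since 0.170 > 0.160.)

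**Step 1: power of the out-of-range count.** With z = [|p2 − p1| − 1.96·√(2p̄(1−p̄)/n)] / √([p1(1−p1) + p2(1−p2)]/n), power = Φ(z). Take the 3.92 SD range and a rise of 0.10 mmol/L at weeks 6 and 26.

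- CV 8%: simulated incidence goes from 6.5% to 9.3%. z = (0.028 − 1.96 × 0.0220)/0.0220 ≈ −0.69, power about 0.24.
- CV 10%: from 8.4% to 11.1%. z = (0.027 − 1.96 × 0.0242)/0.0242 ≈ −0.85, power about 0.20.

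Over all assumed widths and CVs, power is about 0.16–0.37 for a rise of 0.10 and 0.04–0.07 for a rise of 0.05.

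**Step 2: power of a baseline-adjusted comparison at week 26.** SE = residual SD × √(2/300) = residual SD × 0.0816. At CV 8–10% the residual SD is 0.12–0.15, so the SE is 0.0098–0.0122.

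- Rise of 0.10: at worst Φ(0.10/0.0122 − 1.96) = Φ(6.2), about 1.00.
- Rise of 0.05: at worst Φ(0.05/0.0122 − 1.96) = Φ(2.1), about 0.98.

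Over all assumed settings, power is about 1.00 for 0.10 and 0.83–1.00 for 0.05.

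**Step 3: where the loss arises.** Same model, 3.92 SD range, CV 8–10%, rise of 0.10:

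| Event rule | Power |
|---|---|
| any value, either direction | 0.20–0.24 |
| two values required | 0.10–0.11 |
| any value, plus a minimum change of 0.1, 0.2 or 0.3 mmol/L | 0.22–0.33 |
| any value, high only | 0.53–0.54 |

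Confirmation lowers power and a minimum change adds little. Separating the directions more than doubles power, but it still falls well short of comparing the values.

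A second parametrisation shows the cancelling directly. It uses the 3.92 SD range, 60% of variance between patients, and an upward shift of 0.5 SD in all four values. Patients with any high value rise from 6.2% to 16.9% (+10.7 points). Those with low values only fall from 12.3 − 6.2 = 6.1% to 18.5 − 16.9 = 1.6% (−4.5 points). The pooled count therefore moves by only 6.2 points. Power is 0.56 pooled, 0.99 for high values only, and about 1.00 for means.

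**Step 4: events with no drug effect.** At CV 8–10% and 3.92 SD, with three or four tests, 5.5–8.5% of patients have a phosphate event by chance. With a 6 SD range the figure is about 0.5–1.0%. The chance-event rate depends heavily on the assumed width, but the gap in power between Steps 1 and 2 remains at every width.

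**The case against.** Counting new abnormalities among patients who were in range at entry is ordinary safety reporting, and it answers a clinical question that a mean difference does not: how many patients became abnormal. No test or power claim is attached to the count. The full protocol or an analysis plan, neither of which is shown, may add an analysis of the values. All of this stands. It makes the point a gain to be had, not an error in the table.

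A reader might go further and infer that one marginal value is enough for an event, that entry and event limits coincide, and that the lack of a repeat test is therefore the fault, the more so because the discontinuation criteria in {11b} require two tests for phosphate and ALP. The documents do not support this. No counting rule is written. Table 2 gives no numeric entry range, so the identity of the limits is inferred from a shared term. The discontinuation criteria serve a different purpose, and the one for calcium needs only one test. Step 3 shows that requiring two values would make a shift harder to see. Nor does the noise favour either arm: it falls equally on randomised, blinded groups, so it weakens a real difference and cannot create one.

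The alternative also has a limit. Patients who are terminated early are asked under {11b} for calcidiol and calcium only. Week-26 phosphate and ALP may therefore be missing in those with the most abnormal results, and power computed at 300 per arm assumes complete values.

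**Conclusion.** The point holds as a limited one. The incidence is a sound abnormality table, but as the only stated summary it is insensitive to a systematic shift. For phosphate at 300 per arm, power is about 0.16–0.37 against about 1.00 for a rise of 0.10 mmol/L, and 0.04–0.07 against 0.83–1.00 for a rise of 0.05. These figures rest on assumed variability, an any-value count, no surgical shift and complete follow-up. I give no range of figures for ALP or calcium; their endpoints have the same construction, so the mechanism carries over but its size may differ. Priority is low: no primary or secondary conclusion is affected.

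**What to change.** - Keep the out-of-range incidence table for calcium, phosphate and ALP, and report values above and below each range separately.
- For each analyte, add a between-arm difference at week 6 and at week 26 with a 95% CI, from an ANCOVA on the week-0 value (log scale for ALP).
- Do not add a confirmation or minimum-change rule to the event definition for the sake of sensitivity; neither recovers the loss.

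The cost is analysis wording and one extra model per analyte. The week-0, week-6 and week-26 values are already scheduled, so no sample, visit or patient is added and no clinical rule changes. Because week-26 values may be missing after early termination, read that result together with week 6 and the incidence table, and state how many patients contribute to each.
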